# Assessing the implementation and effectiveness of early integrated palliative care in long-term care facilities in France: an interventional mixed-methods study protocol

**DOI:** 10.1186/s12904-023-01157-w

**Published:** 2023-04-06

**Keywords:** Older persons, Early palliative care, Interventional research, Long-term care, Implementation, Quality improvement, Stepped wedge cluster randomised trial

## Abstract

**Background:**

Majority of residents in long-term care facilities (LTCF) have limited and delayed access to palliative care even though many suffer from incurable chronic illnesses that will likely require the provision of palliative care. We present the study protocol of “PADI-Palli”, an intervention aims to advance early integrated palliative care into standard care delivered in LTCF. This study will assess the effectiveness of early integrated palliative care on palliative care accessibility for older persons in LTCF, and identify the key factors for the successful implementation of early integrated palliative care and its sustainability in the LTCF context.

**Methods:**

This multicentre interventional study utilises a pragmatic research design with a convergent parallel mixed-methods approach. The qualitative study will use a case study design and the quantitative study will use a stepped wedge cluster randomised trial. In total, 21 participating LTCF from three French regions will be randomly allocated to one of seven clusters. The clusters will cross over from the usual care to the active intervention condition over the course of the study. The primary outcome relates to the accurate identification of palliative care needs and early access to palliative care for LTCF residents. Secondary outcomes are quality of care, quality of life for residents and their families, and quality of life at work for professionals. Measurements will be performed before and after the intervention. Implementation and evaluation of PADI-Palli intervention is grounded in the Consolidated Framework for Implementation Research.

**Discussion:**

Existing evidence demonstrates that early integrated palliative care in cancer care leads to a significant improvement in patient outcomes and processes of care. Little is known, however, about early integrated palliative care in the context of LTCF for older persons. This study has the potential to fill this gap in the literature by providing evidence on the effectiveness of early integrated palliative care for older persons in LTCF. Moreover, this study will provide a better understanding of the relevant contextual elements that facilitate or hinder early integrated palliative care implementation and transferability. If proven effective, this intervention can be scaled to other care settings in which older persons require palliative care.

**Trial registration:**

ClinicalTrials.gov ID: NCT04708002; National registration: ID-RCB number: 2020-A01832-37.

## Background

The World Health Organization (WHO) and national health authorities such as the French National Authority for Health (HAS) recommend the implementation of an early integrated palliative approach in the care pathway of all patients, including older persons, afflicted by incurable illness [1, 2]. Long-term care facilities (LTCF), known as EHPAD (Établissement d’Hébergement pour Personnes Agées Dépendantes) in France, are admitting a growing number of elderly residents afflicted by advanced chronic pathologies [3], and the majority of these individuals require palliative care services [4]. In France, the number of LTCF residents who die each year represents one quarter of the total annual deaths of all ages [5]. However, despite the number of residents with multiple serious chronic conditions and the high mortality rates in long-term care settings, the provision of palliative care to LTCF residents remains limited and delayed to the last weeks, or even days, before death [6], and palliative care approach is rarely discussed with residents or their families [7].

Non-specialist health professionals working in palliative care are often unaware of the benefits of palliative care for both the patient and their family [8], which results in skills gaps in pain management, advanced care planning, and end-of-life care [9]. Accordingly, the use of specialised palliative care services are introduced late in the trajectory of care, with a median of three to four weeks before death, and even later in geriatric centres, with a median of seven days before death [10]. Moreover, palliative care delivery is often driven by the patient’s diagnosis and subsequent prognosis rather than by the current needs of the patient [11]. Consequently, the deficit of palliative care provision in LTCF leads to the excessive and inappropriate use of acute health services, including emergency visits and unscheduled hospitalizations [12]. Current evidence points to a significant burden of unrelieved symptoms among residents at the end of life [13], and a lack of effective symptom assessment and management [14]. In addition, person-centred care is not adopted and the expectations of relatives are not satisfied, which negatively affects the quality of life of LTCF residents and their families [15]. Finally, care providers in LTCF settings confronted with death situations and complex care needs beyond their competencies are susceptible to psychological stress and a diminished quality of life at work [16].

The WHO defines the palliative care approach as designed to provide person-centred care, respecting personal preferences and human dignity [17]. The palliative care approach focuses on preventing and relieving all dimensions of suffering and maintaining quality of life in the context of incurable and complex pathology [18]. In cancer care, early integrated palliative care allows a better anticipation of the patient’s preference for end-of-life care and a more effective prevention of physical or psychological suffering, therefore increasing quality of life without decreasing survival [19–23]. A study by Nieder and colleagues shows that people who received early integrated palliative care are less often hospitalised in the last three months of life (73% vs. 97%), die less often in the hospital (33% vs. 48%), and have their wishes documented earlier and more thoroughly [24]. According to Hui and Bruera, integrating palliative care early in the care pathway improves symptom control, quality of end-of-life care, caregiver satisfaction, and patient quality of life and satisfaction [25]. However, the provision of palliative care decreases in the absence of cancer or with ageing [26]. In fact, older persons with neurodegenerative diseases rarely benefit from palliative care and research specific to palliative care services for this population is scarce [27].

Despite available evidence on the benefits of palliative care, and various models of early integration of palliative care within the cancer care context, its effectiveness and transferability within the LTCF context for older persons is poorly documented. Furthermore, studies rarely apply an implementation science lens to enhance implementation processes and improve the effectiveness of early palliative care integrated into existing care practices. Thus, only a handful of studies have analysed contextual factors that might mediate the successful implementation of an early integrated palliative care approach within LTCF [28].

To assist in filling this gap, we designed an interventional research model named “PADI-Palli” (Personne Agée Demarche PALLIative Intégrée). Its aims are to advance early integrated palliative care in LTCF to improve palliative care access, prevent and relieve the suffering of older persons, support the best possible quality of life for residents and their families, and improve the quality of life at work for LTCF professionals.

In this study, the following research questions will be addressed: (1) To what extent was the early integrated palliative care model implemented as intended? (2) What were the factors that facilitated and hindered the implementation of early integrated palliative care in LTCF? (3) Does early integrated palliative care contribute to improved timely access to palliative care, quality of care, quality of life of residents, and quality of life at work for LTCF professionals?

Thus, the primary objective of this study is to assess the effectiveness of early integrated palliative care implementation in LTCF in terms of timely access to palliative care for older residents. This study also has two secondary objectives: (1) To identify factors that facilitate or hinder the implementation of early integrated palliative care and its sustainability in the LTCF context, and (2) To assess the effectiveness of early integrated palliative care in LTCF on (a) quality of palliative care services delivered (b) care pathway, (c) quality of life of residents and that of their family caregivers, and (d) quality of life at work for LTCF professionals.

We postulated that early integrated palliative care implementation should support person-centred care practices [29] and strengthen integrated care pathway for residents [27], and as a result improve quality of care and quality of life for LTCF residents and their relatives as well as quality of life at work for LTCF professionals. Therefore, the primary hypothesis addressed in this study is that implementing the early integrated palliative care should improve the timely identification of palliative care needs and access to palliative care for residents in LTCF with serious advanced chronic conditions requiring palliative care provision. The secondary hypotheses are: (1) Implementing early integrated palliative care should improve the quality of care delivered to LTCF residents; (2) Implementing early integrated palliative care should improve the quality of life of residents and their caregivers; and (3) Implementing early integrated palliative care should improve the quality of life at work for LTCF professionals.

## Methods

### Intervention

#### Developing early integrated palliative care tailored to LTCF settings

Addressing the problems related to the challenging nature of palliative situations necessitates an intervention model and implementation methods tailored to their complexity [30]. Therefore, involving all stakeholders in the development of suitable interventions and using a theory-based evidence-driven approach are recommended [31–33]. To develop an appropriate intervention for early integrated palliative care in LTCF, we referenced the Medical Research Council (MRC) framework, which uses four different phases to develop and evaluate complex interventions: development (0-I), feasibility (II), evaluation (III), and implementation (dissemination and long-term follow-up) (IV) [31].

The phases 0 and I started with the identification of existing evidence-based literature for early and integrated palliative care to inform the core of PADI-Palli intervention. The research team ([name]) developed the theoretical components of the intervention and constructed a draft model of early integrated palliative care. We conducted a pilot study from 2017 to 2018 in order to: (1) understand the challenges associated with palliative care in LTCF settings, and (2) test a theoretical model of palliative care implementation appropriate to this context. The research team met with healthcare professionals and managers of 10 LTCF and experts in palliative care to gain an understanding of the situation and needs in LTCF settings to be included as the relevant components of the intervention. These informed the development of the PADI-Palli intervention model with six key components (Table 1). In line with the MRC recommendations, the feasibility of delivering the key elements of the intervention and their acceptability were tested in 10 LTCF (MRC- phase II).

The study protocol reported in this paper is categorized as MRC- phase III, which corresponds to the empirical evaluation of early integrated palliative care, implementation analysis, and effectiveness evaluation in real-world organization of LTCF settings.

**Table 1 Tab1:** Key components and expected outcomes of PADI-Palli intervention model

Key components	Expected outcomes
1: Shared vision of palliative care approach: sharing of experience and existing knowledge, co-creation and application of new knowledge	- Shared views and understanding of palliative care. - Changed previously held (mis)beliefs and acquisition of new knowledge related to palliative care and early integrated palliative care. - Adoption of evidence-based palliative practices.
2: Interprofessional companionship “Compagnonnage”	- Strengthened collaboration within LTCF. - Improved palliative care practices at individual and collective levels. - Improved quality of life at work for healthcare professionals.
3: Use of validated tools for clinical assessment (identification and patient needs assessment)	- Improved knowledge and utilization of validated tools for the assessment of palliative care needs in older persons.
4: Early pro-active identification	- Improved knowledge and utilization of validated tools for the pro-active identification of residents who may benefit from early palliative care.
5: Advance care planning	- Change of misconception of residents and their caregivers towards palliative care. - Improved quality of care. - Improved quality of life for older persons and their caregivers.
6: Interprofessional and intersectoral collaboration between health and medical-social fields/services	- Enhanced partnership between LTCF, hospitals, and specialist palliative care teams. - Improved quality of life at work and reduced distress for professionals in relation to end-of-life care management.

#### Implementation strategy

As recommended in the implementation sciences, we adopted an implementation framework for enhancing implementation effectiveness [34] and for understanding the conditions necessary to support the introduction of PADI-Palli intervention, all the while meeting specific local situation and setting requirements [35]. Thus, implementation and evaluation of PADI-Palli intervention are grounded in the Consolidated Framework for Implementation Research (CFIR) [36]. The CIFR is regarded as a helpful theoretical framework for implementation research on healthcare service delivery as it allows for the consideration of specific determinants that can influence implementation outcomes and the assessment of implementation effectiveness under five domains: intervention characteristics, outer setting, inner setting, characteristics of individuals, and process [34]. Given that everyday micro-level components of clinical practice, organizational dynamics within LTCF, and external factors can potentially influence the effectiveness of the palliative care approach, these factors should be considered as a whole system [35].

To reach the expected change goals at these different levels and facilitate the implementation, analysis, and transferability of PADI-Palli intervention, our implementation strategy is informed by Rogers’ theory of innovation decision process [37]. According to this theory, the characteristics of implementation settings at individual and system levels, the existing knowledge and practices, and the stakeholders’ expectations should be considered throughout the decision-making process and intervention implementation.

The implementation is categorized into three periods with six overall steps. Period one (pre-implementation) includes two steps, identification and engagement of participants and evaluation of the current state in terms of palliative care practices, professional competencies, palliative care needs, and organisational characteristics; period two (implementation) has two steps, intervention delivery and consolidation; and period three (post-implementation) with two steps, autonomy and sustainability.

### Process evaluation design: a parallel mixed-methods approach

This study is a multicentre interventional research using a pragmatic study design [38] with a convergent parallel mixed-method approach [39] (Fig. 1). The qualitative component of the study follows a case study methodology [40], and the quantitative component of the study involves a stepped wedge cluster randomised trial (SW-CRT) [41].

The clusters will cross over from the usual to the active intervention condition during the trial, according to a randomised schedule. This design is adapted to collect intervention data and is used to evaluate an intervention during routine implementation [42]. While cluster randomisation addresses the problem of contamination bias, staggering the intervention among clusters controls for temporal drift and facilitates the logistics of implementation and data collection [43]. The principle that all study sites will benefit from the intervention is an important motivator that contributes to the feasibility of this study.

**Fig. 1 Fig1:**
[figure not shown]
Flowchart representing the research design with a convergent parallel mixed-method

As depicted below in Fig. 2, over the course of the study timeline each of the 21 participating centres will be defined as a cluster and randomly allocated to one of the seven groups. This allocation will follow a sequence similar to the observational and interventional periods. Randomisation of LTCF will be stratified by region; each group includes LTCF from the three participating regions.

The strategy used addresses issues related to incomplete design by minimizing the collection load to preserve good power by removing uninformative combinations of clusters and periods without too much alteration of the power [44]. A sequence includes: one or two pre-intervention observational periods of two months; one delivery intervention period of three months followed by an interventional consolidation period of three months; then a short-term observational period of two months; and 12 months after intervention a final observational period of two months, called autonomy.

The individual data collection is based on an open cohort: as the study progresses, some residents will leave the LTCF or die (on average 25% each year, but likely higher for subjects requiring palliative care), while others will be admitted to the LTCF or begin to require palliative care and will be included at a later date.

**Fig. 2 Fig2:**

Stepped wedge with seven cluster groups and periods of measurements. The clusters were randomly assigned to seven groups (One Cluster = 1 LTCF) that crossover to receive the intervention after pre-intervention measurements (one to two measurements).

### Outcome evaluation

#### Primary outcome measures

The primary outcome measures relate to the accurate identification of palliative care needs and early access to palliative care for residents in LTCF context. These will be assessed through a comparison of the pre- and post-intervention periods, with the main comparison focusing on the latest evaluation (autonomy). The following will be measured and compared:

1) Identification sensitivity: This main criterion is the proportion of residents identified by the LTCF team as in need of palliative care among those with “potential” palliative care needs identified proactively by a dedicated research nurse using “Gold Standards Framework Proactive Identification Guidance” [45] and the Palliative Care Indicator Tool (PICT) [46].

2) Access: The proportion of residents with effective access to palliative care delivery among those identified as in need of palliative care (with or without referral to the specialist palliative care service).

3) Optimal timing: We postulate that during the pre-intervention phase, the identification of residents’ palliative care needs is delayed and may not be systematically followed by the delivery of palliative care. Therefore, we will estimate the time gain by focusing on the interval between the time residents are identified as in need of palliative care and the time of their death (or discharge, withdraw from follow-up). An increase in this time can be interpreted as a shortening of the identification delay but also as an extension of the delivery period of palliative care and the identification of the need for palliative care, both of which would support the effectiveness of palliative care.

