#### Primary outcome analysis

The data analysis will be based on the comparison of data collected during pre-intervention versus post-intervention periods. The three primary criteria will be tested according to a hierarchical procedure: identification sensitivity, access, and optimal timing from a fixed sequence procedure; constructed using a pre-specified sequence of hypotheses; and endpoints ordered according to their importance [62]. All tests will be performed at the 0.05 level following the pre-specified order. Once one hypothesis is tested and the results indicate it is not significant, all subsequent tests will not be performed.

The statistical model will take into account the non-independence of the observations, as multiple evaluations may concern the same resident across time due to the use of open cohorts and several residents are included from the same LTCF. This hierarchy (three levels) leads to the use of generalized linear mixed models (GLMM) for repeated measures [63]. For dichotomous outcomes (i.e. the patient has been identified or not), we will use a Bernoulli distribution with a logistic link function, and for continuous outcomes a normal distribution with identity link function. The independent variables will be: the LTCF and the resident considered as random factors, the calendar time interval (common to all groups) considered as a fixed factor, and treatment mode for the cluster in the time interval (pre-intervention = control, post-intervention = experimental) considered as a fixed factor associated with the effect of the intervention. The chronological sequence of stepped wedge randomized trials means that the number of clusters exposed to the intervention being tested increases as the trial progresses [41].

The observation of an intervention effect may reflect the existence of an underlying secular trend that is independent of the intervention. Therefore, modelling the background secular trend is necessary to remove bias in estimating the effect attributed solely to the intervention. However, the saturated time parameterization (by J-1 indicators if there are J periods) may not be the most efficient approach if there are a large number of periods relative to the number of waves and clusters due to the reduced degree of freedom available for estimating the intervention effect. Thus, we will use a parsimonious specification with a minimum number of parameters, such as a polynomial specification to a fixed degree [64].

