#### Secondary outcome analysis

Multilevel multivariate models will be constructed and validated as in the analysis of the primary outcome analysis. The survival time of residents will be analysed by a Cox model including a delayed input, a temporal axis representing age of admission in LTCF as its origin, and the situation with respect to the intervention coded by a time-dependant variable.

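### Criterion 3 (optimal timing) mixes identification delay with survival, so an increase alone cannot show that palliative care needs were identified earlier

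*Protocol article*

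**What the plan says.** In the protocol article, Primary outcome measures, item 3 (Optimal timing) defines the time gain through the "interval between the time residents are identified as in need of palliative care and the time of their death (or discharge, withdraw from follow-up". It then gives two readings of a longer interval. The first is "An increase in this time can be interpreted as a shortening of the identification delay". The second follows in the same sentence: "but also as an extension of the delivery period of palliative care". The sentence ends by saying of these readings "both of which would support the effectiveness of palliative care". Longer survival is not named as a possible explanation.

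Primary outcome analysis gives the criterion confirmatory status: "The three primary criteria will be tested according to a hierarchical procedure", with optimal timing third. The model described there has LTCF and resident as random factors, and calendar time and treatment mode as fixed factors.

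Secondary outcome analysis adds: "The survival time of residents will be analysed by a Cox model including a delayed input", with "the situation with respect to the intervention coded by a time-dependant variable". The plan therefore estimates an intervention effect on survival. It does not connect that estimate to the reading of criterion 3.

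The Background reports that in cancer care early integration works by "therefore increasing quality of life without decreasing survival". The article nowhere says that survival is assumed unchanged in long-term care.

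**The concern.** The primary objective and hypothesis concern timeliness: residents should be identified, and reach palliative care, sooner. A clock that starts at identification and stops at death moves when either end moves. A resident identified on the same date who lives longer has not been identified sooner, yet the longer interval would count in favour of the intervention. Conversely, if survival shortened, a true reduction in delay could be masked or reversed.

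The calendar-time term can absorb a mortality trend common to all sites. It cannot absorb an effect of the intervention itself on survival, because that effect falls into the treatment coefficient. At stake is the third primary conclusion. The first two criteria are unaffected.

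**Working it through.** The protocol gives no effect size, standard deviation or power for criterion 3, so there is no stated figure to reproduce. The check has three parts.

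**1. Identity.** Let N be the onset of need, I team identification and D death. For a resident followed to death:

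D − I = (D − N) − (I − N) = survival from need − identification delay.

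Only the second term is the delay that the hypothesis concerns.

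**2. Can the criterion tell the two apart?** This was simulated with 2,000,000 residents per scenario. The assumptions were a fixed delay from need to identification, Weibull survival, and no discharge, withdrawal or administrative censoring. Mean interval among identified residents, in months:

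| One-year death risk, hazard shape | Delay 6, HR 1 | Delay 6, HR 0.8 | Delay 6, HR 1.25 | Delay 3, HR 1 |
|---|---|---|---|---|
| 25%, rising (shape 2) | 15.0 | 17.2 | 13.0 | 17.1 |
| 50%, rising (shape 2) | 8.5 | 9.8 | 7.2 | 10.3 |
| 25%, constant (shape 1) | 41.7 | 52.1 | 33.4 | 41.7 |
| 50%, constant (shape 1) | 17.3 | 21.6 | 13.9 | 17.3 |

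In the first row, a hazard ratio of 0.8 with no change in delay (15.0 to 17.2) looks almost the same as truly halving the delay (15.0 to 17.1). Under a constant hazard, halving the delay leaves the mean among identified residents unchanged, while a survival effect moves it. The HRs, shapes, delays and the 50% risk are assumptions chosen to show the mechanism. They are not predictions.

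**3. Size over a realistic horizon.** The untruncated means above exceed what this study can observe. One site's sequence takes 22 to 24 months: 2 or 4 months before the intervention, 3 + 3 months of delivery and consolidation, and a final 2-month period 12 months after the intervention (2 or 4 + 6 + 12 + 2). Restricted means at 12 and 24 months are therefore more relevant.

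Inputs: the design section gives average annual loss of 25%, deaths and departures combined, and says it is probably higher in residents needing palliative care. A range of 25% to 50% is assumed. The hazard is taken as constant and identification dates as unchanged.

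Monthly hazard λ = −ln(1 − q)/12, which is 0.02397 at q = 25% and 0.05776 at q = 50%.

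Restricted mean to t months = (1 − e^(−λt))/λ. A 10% lower hazard replaces λ by 0.9λ.

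| q | t (months) | HR 1 | HR 0.9 | Difference |
|---|---|---|---|---|
| 25% | 12 | 10.43 | 10.57 | 0.14 months (about 4 days) |
| 50% | 12 | 8.66 | 8.93 | 0.27 months (about 8 days) |
| 25% | 24 | 18.25 | 18.73 | 0.48 months |
| 50% | 24 | 12.98 | 13.71 | 0.73 months |

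For scale, the Background puts the introduction of specialist palliative care at a median of three to four weeks before death, and seven days in geriatric centres. That is only a proxy, because criterion 3 starts at team identification and access does not require specialist referral.

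**The case against.** A reader might infer that the protocol treats every survival change purely as a shorter delay. The text does not support that. The same sentence offers a longer delivery period as a second reading, and longer life under palliative care would literally extend delivery. Shorter survival would look like a longer delay, not a shorter one. What remains is that the two readings are not separated, and that both are credited to an intervention whose stated primary aim is timeliness.

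A reader might also infer a large artefact. Untruncated exponential means are 41.7 months at 25% annual loss and 17.3 at 50%, so a 10% lower hazard (mean divided by 0.9) would add 4.6 or 1.9 months, more than the whole usual-care lead. The documents do not support this either. The 25% includes departures, the study cannot observe such means, and a constant-hazard mean of 17 to 42 months from identification is incompatible with a lead of days to weeks. The restricted figures are the defensible ones.

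Two further points have weight. If usual-care identification is triggered by nearness to death, as the Background suggests for care provision, longer survival would shift identification as well and the interval would change less. The planned Cox model could also reveal a survival shift, so its presence is no contradiction. But nothing ties its result to the interpretation of criterion 3.

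Replacing the criterion outright with time from nurse flag to team identification is not clearly better. Flags arise in discrete measurement periods, the measure overlaps with criterion 1, and it discards lead time gained before the flag.

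**Conclusion.** The concern holds as a problem of interpretation. An increase in criterion 3 cannot on its own be read as earlier identification, and the absence of an increase cannot rule it out. The identity behind this needs no distributional assumption.

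The size does rest on assumptions: constant hazard, 25% to 50% annual loss, identification dates unaffected, and a 10% hazard reduction for which the documents give no evidence in either direction. On those terms the shift is about 4 to 8 days over 12 months and 0.5 to 0.7 months over 24. That is modest, but not negligible if baseline leads are short.

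Criterion 3 is last in the fixed sequence, so the main criterion, identification sensitivity, is untouched. The point deserves correction because the protocol itself fixes how a primary result is to be read.

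**What to change.** Keep criterion 3 and make three changes.

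- Reword item 3 of Primary outcome measures so that an increase alone is not taken as a shorter identification delay, and name a change in survival as an alternative explanation.
- Pre-specify two supporting analyses by phase in residents flagged by the research nurse: (i) nurse flag to team identification, with death as a competing event; (ii) nurse flag to death.
- State that earlier identification will be claimed only if (i) supports it and (ii) does not explain the increase.

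The cost is a text change to a primary criterion's interpretation and a little more analysis. The flag date is a coarse origin because it is tied to the measurement periods. The article does not say that flag dates are recorded, so this should be confirmed first.
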